## Methods: patient and public involvement, and trial design

### Patient and public involvement {11}

Patients are included in the study to complete the 6-week study phase, as well as the preliminary and post-examination and follow-up. If members of the training groups are using the Mini Stability Trainer or the Wobble Smart Board, it is imperative that they complete the training sessions during the study phase. The study also includes members of the public, students, physiotherapists, and various sports groups to establish contact between patients and study employees.

### Trial design {12}

This study protocol follows the “Standard Protocol Items: Recommendations for Interventional Trials (SPIRIT) 2013 Statement” (https://www.equator-network.org/reporting-guidelines/spirit-2013-statement-defining-standard-protocol-items-for-clinical-trials/). The study is a prospective, single-center, interventional, randomized controlled trial with an intervention group (forefoot and rearfoot stability training) and two comparison groups, either a usual balance training group or a control group. It is a single-blind (principal investigator) design with patients randomized 1:1:1 to one of the three parallel groups. To ensure internal validity, a control group is included that does not receive any balance training intervention. Because many patients with CAI do not seek medical or physical therapy and continue with their usual activities, participants in the control group are allowed to do so. A summary of study information is presented in Table 1.

**Table 1 Tab1:** Study information

Category	Information
Country	Germany
Intervention	Active part: 6 weeks of training with the Mini Stability Trainer according to a predefined exercise schedule; 6 weeks of training with the Wobble Smart Board according to a predefined exercise schedule; one training session is performed under the supervision of a member of the study team, at least 17 training sessions are performed independently by each subject at home Control group: activities of daily living and sports activities; balance exercises are not allowed
Inclusion and exclusion criteria	Inclusion criteria: age between 18 and 44 years; based on the guidelines of the International Ankle Consortium: history of at least one ankle injury more than 1 year ago with typical signs of inflammation; self-reported ankle instability; in addition, two or more episodes of “giving way” must have occurred within the previous 6 months; Cumberland Ankle Instability Tool (CAIT ^a^) score ≤ 24 (in the case of bilateral ankle instability, the more severely affected side is selected) Exclusion criteria: acute injury, surgery or fracture of the lower extremity, neurological disorders, chronic overuse injuries such as Achilles or patellar tendinopathy; current participation in a targeted ankle rehabilitation program
Study type	Allocation: randomized; model: parallel allocation; intervention description: comparison of clinical outcome measures at four time points between three cohorts (Wobble Smart Board, Mini Stability Trainer, control group) of subjects with chronic ankle instability (CAI ^b^), whether the two intervention groups reduce the primary and secondary outcome measures compared to the control group; blinding: single-blind; blinding description: the principal investigator analyzing the results will be blinded to group allocation; different investigators will be used to perform the intervention and to analyze the results
Primary outcomes	Dynamic balance and postural stability using the Y-Balance Test (YBT ^c^) and Modified Balance Error Scoring System (MBESS d)
Secondary outcomes	Gait biomechanics using 3D gait analysis (e.g., ankle abduction and adduction; knee varus/valgus position; spatiotemporal parameters); ankle function using the Foot and Ankle Ability Measure (FAAM ^e^)

^a^*CAIT *Cumberland Ankle Instability Tool; ^b^*CAI *chronic ankle instability; ^c^*YBT *Y-Balance test; ^d^*MBESS *Modified Balance Error Scoring System; ^e^*FAAM *Foot and Ankle Ability Measure

## Methods: participants, interventions, and outcomes

### Trial setting {13}

The present study is being conducted at the Movement Laboratory of the Faculty of Health Care at Niederrhein University of Applied Sciences in Krefeld, Germany. The Movement Laboratory is equipped with a 10-m-long walkway with two integrated force plates (Bertec, version 1.0.0., Bertec Corporation, Columbus, OH, USA). A motion analysis system with 10 cameras (Qualisys, Göteborg, Sweden) is also available for motion analysis. Characteristics of the people who are needed for the trial are presented in Table 2.

**Table 2 Tab2:** Characteristics of the people who are needed for the trial

Characteristic	The people we would expect to see included
Age	18 to 44 years
Sex	Male, female, and intersex
Gender	Man and woman together with any other gender identities
Race, ethnicity, and ancestry	Patients with CAI from all races, ethnicities, and ancestries are eligible to participate in the study
Socioeconomic status	Patients with CAI from all socioeconomic status are eligible to participate in the study
Geographic location	Patients with CAI from all geographic locations are eligible to participate in the study, but have to carry out the preliminary examination and post-examination in the Movement Laboratory
Other characteristics relevant to the trial	Not applicable

### Eligibility criteria for participants {14a}

To be eligible for the study, patients must meet the following predefined inclusion criteria:Age between 18 and 44 yearsHistory of at least one ankle injury ≥ 12 months ago with typical signs of inflammationSelf-reported ankle instabilityTwo or more episodes of “giving way” within the previous 6 monthsCumberland Ankle Instability Tool (CAIT) score ≤ 24 (in the case of bilateral ankle instability, the more severely affected side is selected)

Exclusion criteria are the following:Acute injuryLower extremity surgery or fractureNeurological diseaseChronic overuse injuries such as Achilles or patellar tendinopathyCurrently participating in a targeted ankle rehabilitation program

### Eligibility criteria for sites and those delivering interventions {14b}

No additional centers or intervention providers are required for the study. The preliminary examination and post-examination are conducted exclusively in the Movement Laboratory of the Faculty of Health Care at Niederrhein University of Applied Sciences in Krefeld, Germany.

### Who will take informed consent? {32a}

The physiotherapist AB obtains the informed consent before the preliminary examination.

### Additional consent provisions for collection and use of participant data and biological specimens {32b}

Additional consents for the collection and use of participant data are included in the informed consent form and are obtained by AB prior to the preliminary examination. No biological samples are used in this study.

• Place hands on iliac crest • Step the affected foot forward on the Mini Stability Trainer (forefoot on the green plate/rearfoot on the blue or yellow plate with tilt to the left and right) • Look forward • Shift weight evenly to front foot with knee slightly flexed and hold for 20 s (opposite foot maintains light contact with floor with big toe) • Rest for 30 s • Repeat with opposite foot • Repeat 5 times for each side	• Place hands on iliac crests • Step forward with the affected foot onto the center of the Wobble Smart Board (difficulty level according to your own ability) • Look forward • Shift weight evenly to front foot with knee slightly flexed and hold position for 20 s (opposite foot maintains light contact with floor with big toe) • Rest for 30 s • Repeat with opposite foot • Repeat 5 times for each side
Two-minute rest after exercise 1 Exercise 2	
• Place hands on iliac crest • Step with the affected foot to the side on the Mini Stability Trainer (forefoot on the green plate/rearfoot on the red plate with inclination in all directions) • Look forward • Shift weight evenly to affected foot with knee slightly flexed and hold position for 20 s (opposite foot maintains light contact with floor with big toe) • Rest for 30 s • Repeat with opposite foot • Repeat 5 times for each side	• Place hands on iliac crest • Step with the affected foot from the side to the center of the Wobble Smart Board (difficulty level according to your own ability) • Look forward • Shift weight evenly to affected foot with knee slightly flexed and hold position for 20 s (opposite foot maintains light contact with floor with big toe) • Rest for 30 s • Repeat with opposite foot • Repeat 5 times for each side

**Table 4 Tab4:** Schedule for the two exercise groups (Mini Stability Trainer; Wobble Smart Board) for weeks 3 and 4

Mini Stability Trainer	Wobble Smart Board
For each week of training 3 × per week with a minimum of 1 day and a maximum of 2 days rest in between	
Weeks 3 + 4	
Exercise 3	
• Place hands on iliac crest • Step forward with affected foot on Mini Stability Trainer in one-legged stance with knee slightly flexed (forefoot on the blue or yellow plate with inclines to left and right/rear foot on the green plate) • Look forward • Hold position for 25 s (opposite foot off the floor) • Rest for 30 s • Repeat with opposite leg • 5 times each side total	• Place hands on iliac crest • Step forward with the affected foot onto the center of the Wobble Smart Board in a one-legged stance with the knee slightly flexed (increase the difficulty by 1 from the first 2 weeks of training) • Look forward • Hold position for 25 s (opposite foot off the floor) • Rest for 30 s • Repeat with the opposite leg • 5 times each side total
Two-minute rest after exercise 3 Exercise 4	
• Place hands on iliac crest • Step with the affected foot to the side on the Mini Stability Trainer in a one-legged stance with the knee slightly flexed (forefoot on the red plate with tilt in all directions/rearfoot on the green plate) • Look forward • Hold position for 25 s (opposite foot off the floor) • Rest for 30 s • Repeat with opposite leg • 5 times each side total	• Place your hands on pelvic crest • Step the affected foot from the side to the center of the Wobble Smart Board in a one-legged stance with the knee slightly bent (increase the difficulty by 1 compared to the first 2 weeks of training) • Look forward • Hold position for 25 s (opposite foot off the floor) • Rest for 30 s • Repeat with opposite leg • Repeat 5 times for each side

**Table 5 Tab5:** Schedule for the two exercise groups (Mini Stability Trainer; Wobble Smart Board) for the last 2 weeks

Mini Stability Trainer	Wobble Smart Board
The following applies for each training week: 3 × per week with at least one day and a maximum of 2 days rest in between	
Weeks 5 + 6	
Exercise 5	
• Place hands on iliac crest • Step forward on the Mini Stability Trainer with the affected foot in a one-legged stance with the knee slightly flexed (forefoot on the red plate with tilt in all directions/rearfoot on the green plate) • Look forward • Hold position for 30 s (opposite foot off the floor) • Rest for 30 s • Repeat with opposite leg • 5 times each side total	• Place hands on iliac crest • Step forward with the affected foot to the center of the Wobble Smart Board in a one-legged stance with the knee slightly flexed (increase difficulty by 1 compared to both training weeks 3 + 4) • Look forward • Hold position for 30 s (opposite foot off the floor) • Rest for 30 s • Repeat with opposite leg • 5 times each side total
Two-minute rest after exercise 5 Exercise 6	
• Place hands on iliac crest • Step with affected foot to the side on the Mini Stability Trainer in one-legged stance with knee slightly flexed (forefoot on the red plate with tilt in all directions/rearfoot on the green plate) • Look forward • Hold this position for 30 s (opposite foot off the floor) and tap the floor alternately with the opposite foot forward, to the side, and backward • Rest for 30 s • Repeat with opposite leg • Repeat 5 times for each side	• Place hands on iliac crest • Step with the affected foot from the side to the center of the Wobble Smart Board into a one-legged stance with the knee slightly flexed (increase the difficulty by 1 compared to both training weeks 3 + 4) • Look forward • Hold this position for 30 s (opposite foot off the floor) and tap the floor alternately with the opposite foot forward, to the side, and backward • Rest for 30 s • Repeat with opposite leg • 5 times each side total

Participants may withdraw from the study at any time without giving a reason. If patients are unable to perform a test during laboratory measurements or home exercise, or if they need to deviate from the prescribed exercise plan, this will be documented and taken into account in data analysis and interpretation. If a participant is required to receive the other group’s treatment or to switch to the control group (e.g., experiencing significant pain during exercise), or if values are missing for any reason (e.g., dropout or loss to follow-up), this is accounted for using intention-to-treat (ITT) analysis.

### Criteria for discontinuing or modifying allocated intervention/comparator {15b}

The criteria for terminating or modifying the intervention or comparison are pain with signs of inflammation during or after the training sessions, as well as illnesses that prevent training.

### Strategies to improve adherence to intervention/comparator {15c}

After randomization to one of the two intervention groups, the participants receive the appropriate training device for the respective intervention with detailed training instructions from the physiotherapist (AB). In addition, they receive a training booklet with all exercise modalities (Tables 3, 4, and 5). As previously mentioned, a supervised training session is conducted in the laboratory by the physiotherapist to instruct and familiarize the participant with the exercises. To ensure adherence with the home training, each participant is instructed to check a box in the training booklet after each session. Participants are also asked to document any peculiarities, such as pain or other symptoms, that may have occurred during the exercise. During the study, participants can contact the physiotherapist at any time via email or once a week via Zoom to clarify any questions they may have. Each participant gets financial compensation (20 €) after the second laboratory measurement after 6 weeks. Participants are informed that they may engage in their usual activities, including sports, but that additional balance or sensorimotor training is not permitted during the trial, including follow-up. Participant insurance is provided to all study participants. However, there is no provision for post-trial care.

### Concomitant care permitted or prohibited during the trial {15d}

Due to CAI, treatments such as physiotherapy, medication, and drug therapy are not permitted. Special balance training for the ankle is also prohibited. Participants may engage in all activities of daily living (ADL) and sports activities, including training sessions.

### Ancillary and post-trial care {34}

Participants have the opportunity to liaise with physiotherapist AB via email during and after the program. Additionally, the program incorporates weekly meetings that can be conducted via Zoom.

### Outcomes {16}

#### Primary outcome measurements

##### Y-Balance Test

The Y-Balance Test (YBT) is a test of dynamic balance and is administered using a standardized test kit [25, 26]. In this study, the participant stands barefoot with the test leg on the stance platform of the test kit with the most distal portion of the big toe at the starting line. The hands are placed on the left and right iliac crest. The participant is instructed to move the target (reach indicator) with the free leg along the pipe as far as possible in the anterior, posteromedial, and posterolateral directions and to hold the end position for 3 s. Six trials are performed in each direction [27]. The first 3 trials are used to familiarize the participant with the task. The following 3 trials are recorded from the tape measure (5 mm increments) of each pipe at the edge of the reach indicator, at the point where the most distal point of the foot reaches, and used for further analysis. The participant is instructed to maintain balance during the trials and to return to the starting position after each trial. A trial is considered invalid and will be repeated if the participant touches the ground with the free leg, slips with the standing foot, falls off the stance platform, loses contact with the reach indicator while moving it to the maximum reach position, kicks the reach indicator forward, places the foot on the top of the reach indicator, or fails to return to the starting position under control. The maximum number of attempts is 3. The left leg is measured first. In addition, leg length is measured from the anterior superior iliac spine to the medial malleolus with the participant in the supine position to normalize anterior, posteromedial, and posterolateral reach distances to leg length. The following formula is used for normalization: reach distance/leg length × 100. The means of these normalized values are then calculated. In addition, the composite score is calculated using the following formula: (sum of the 3 reach distances)/3 times leg length × 100. In this study, the results are presented using the composite score. The minimum detectable change in YBT is between 7.7 and 14% [28]. The difference in change between the groups is assessed and calculated using parametric statistical analysis. The aggregation method is mean ± SD, and the measurements are taken before and after the 6-week intervention.

##### Modified Balance Error Scoring System

In this study, the Modified Balance Error Scoring System (MBESS), which measures static balance, is performed on a foam surface (Balance Pad, ARTZT vitality®, Ludwig ARTZT GmbH, Dornburg, Germany) [29]. To perform the test, the participant stands in three positions on the balance pad with hands on the left and right iliac crest, eyes closed, and attempts to maintain the position for 20 s. Balancing in each of the three stance positions is scored out of a maximum of 10 points each. Errors are subtracted from the score, resulting in a maximum total MBESS score of 30 [30]. Errors are scored if the eyes are opened, the hands are removed from the pelvis, a step, trip, or fall occurs, hip abduction or flexion exceeds 30°, or the forefoot or heel is lifted. If the participant can hold the position for less than 5 s, the position is penalized with ten penalty points [31]. Reliability of the MBESS is moderate to strong with coefficients ranging from r = 0.6–0.88 [30]. The difference in change between groups is assessed and calculated using nonparametric statistical analysis. The aggregation method is median and interquartile range, and measurements are taken before and after the 6-week intervention.

#### Secondary outcome measurements

##### Function of the ankle joint

The German version of the Foot and Ankle Ability Measure (FAAM) questionnaire is a validated patient-reported outcome measure to identify functional limitations in individuals with CAI [32–34]. Twenty-one items relate to the Activities of Daily Living (ADL) subscale (FAAM-ADL) and eight items relate to the Sport subscale (FAAM-Sport) [35]. For each item, the possible responses range from 0 “no problems” to 4 “unable to do anything.” The score for each item in each subscale is summed (maximum score for the ADL subscale = 84; maximum score for the Sport subscale = 32). The sum is divided by the maximum score and then multiplied by 100. A resulting maximum score of 100 represents no functional limitation in each subscale. In patients with chronic ankle instability, FAAM-ADL and FAAM-Sport scores of <90 and <80, respectively, are considered to represent functional disability. The questionnaire is also suitable for recording changes over time. The minimum detectable change (MDC) is ±5.7 points for the ADL subscale and ±12.3 points for the Sport subscale [35]. The difference in change between groups is assessed and calculated using nonparametric statistical analysis. The aggregation method is median and interquartile range, and measurements are taken before and after the 6-week intervention, as well as at the 4- and 12-week follow-ups.

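### The FAAM item anchors run in the opposite direction to the scoring formula, the stated meaning of 100 and the disability cut-offs; taken literally, every subscale score becomes 100 minus the intended score

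*Protocol article*

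**What the plan says.** The scoring rule is in the Protocol article, Outcomes {16}, under Function of the ankle joint. It has five parts.

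- Item anchors: "For each item, the possible responses range from 0 “no problems” to 4 “unable to do anything".
- Item counts: "Twenty-one items relate to the Activities of Daily Living (ADL) subscale (FAAM-ADL) and eight items relate to the Sport subscale (FAAM-Sport").
- Summation: "The score for each item in each subscale is summed (maximum score for the ADL subscale = 84; maximum score for the Sport subscale = 32").
- Transformation: "The sum is divided by the maximum score and then multiplied by 100".
- Interpretation: "A resulting maximum score of 100 represents no functional limitation in each subscale", followed by the cut-offs, "FAAM-ADL and FAAM-Sport scores of <90 and <80, respectively, are considered to represent functional disability".

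The same paragraph gives minimum detectable changes of ±5.7 points (ADL) and ±12.3 points (Sport). Statistical methods {27a} assigns the FAAM to Friedman or Kruskal-Wallis tests with Bonferroni-corrected post hoc tests. Participant timeline {18} and Table 6 show the FAAM as the only assessment at 4 and 12 weeks after the intervention.

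Table 1, under Trial design {12}, describes the comparison as "whether the two intervention groups reduce the primary and secondary outcome measures compared to the control group".

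**The concern.** The anchors make a high item score bad. The formula preserves that order, because it only sums and rescales. The interpretation and the cut-offs make a high total good. No reversal step appears in this paragraph or elsewhere in the article, so anyone who scores the forms from the published text gets the opposite of the stated meaning.

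The FAAM is the only patient-reported outcome (the CAIT is collected for eligibility and baseline only) and the only source of information after the 6-week measurement. If it were scored literally and then read with 100 as the best state, all follow-up results would be reported with the wrong direction: benefit would look like deterioration, and deterioration like benefit.

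The data checks described would not necessarily reveal this. Data management {26} relies on referential and range checks, and a reversed score still lies between 0 and 100.

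**Working it through.** **Inputs** (all from Function of the ankle joint): 21 ADL items and 8 Sport items; responses 0 (best) to 4 (worst); score = sum / maximum × 100; 100 = full function; cut-offs 90 (ADL) and 80 (Sport).

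**1. Reproduce the stated maxima.** 21 × 4 = 84 and 8 × 4 = 32. Both agree with the article, so the formula is being read as intended.

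**2. Apply the rule as written, and then with each response reversed (4 − x).**

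| Responses | ADL as written | Sport as written | Either subscale, reversed |
|---|---|---|---|
| All 0 (no difficulty) | 0/84 × 100 = 0 | 0/32 × 100 = 0 | 100 |
| All 1 (one step of difficulty on every item) | 21/84 × 100 = 25 | 8/32 × 100 = 25 | 75 |
| All 4 (complete inability) | 84/84 × 100 = 100 | 32/32 × 100 = 100 | 0 |

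With n items, the reversed score is (4n − sum)/4n × 100 = 100 − score. Only the reversed column agrees with the stated meaning of 100.

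**3. Cut-offs.** As written, an ADL score under 90 means a raw problem sum below 0.90 × 84 = 75.6, and a Sport score under 80 means a sum below 0.80 × 32 = 25.6. A symptom-free participant (sum 0) is therefore labelled disabled and a wholly incapacitated one (84 or 32) is not. After reversal, disability means a problem sum above 0.10 × 84 = 8.4 (ADL) or 0.20 × 32 = 6.4 (Sport), which is the sensible order. The cut-offs therefore side with the stated meaning of 100, and the anchor sentence is the odd one out.

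**4. Change scores.** (100 − post) − (100 − pre) = −(post − pre). A participant who goes from one step of difficulty on every item to none moves from 75 to 100 on the intended scale (+25) and from 25 to 0 as written (−25). The absolute size is the same, so a threshold stated as ±5.7 or ±12.3 is met or missed equally often.

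**5. Planned tests.** Replacing every value x by 100 − x turns rank R into N + 1 − R (Kruskal-Wallis, N observations) or k + 1 − R (Friedman, k time points). The omnibus statistics depend on squared deviations of rank sums or mean ranks from their expected value, so they do not change. A numerical check with three simulated groups of 12 gave H = 0.621 and p = 0.733 on both scales. This invariance requires that all forms be reversed alike.

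**The case against.** The best defence is that this is a wording slip in one sentence. The intended direction is recoverable, because the article fixes it twice: by the meaning of 100 and by the cut-offs. The instrument is the validated German version, completed on prepared sheets (Plans for assessment and collection of outcomes {25a}), and those sheets may well be coded correctly. The FAAM is secondary. Primary outcomes are the YBT and MBESS, and the sample size rests on the YBT composite. The cut-offs drive nothing operational: eligibility uses the CAIT, and {27a} plans no responder analysis.

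All of that stands, and it rules out several stronger readings that a reader might infer:

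- *The trial's FAAM data are reversed.* The article does not show how the sheets, Word documents or Excel file code the items, so this cannot be known.
- *The FAAM tests would be invalid.* Consistent reversal leaves the omnibus p-values unchanged.
- *The minimum detectable change has the wrong direction.* It is stated as a symmetric ± value and has none.
- *The meaning of 100 is the error.* That sentence agrees with the cut-offs; the anchors are what conflict.
- *Table 1 shows that the trial aims in the wrong direction.* Objectives {10} and the Discussion both speak of improvement, so the table cell is loose wording in a summary.

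The defence does not remove the contradiction. The article sets out a complete scoring algorithm that gives the reverse of its own stated result, which is different from leaving a detail to another document. Unchanged p-values are also no protection: a significant result would remain significant and be read the wrong way round.

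**Conclusion.** The point holds as an internal contradiction in the FAAM scoring paragraph. It is certain on the page and needs no outside source. If the anchors and formula are applied literally, every subscale score equals 100 minus the intended score. What reverses is the sign of change, the meaning of the medians and the cut-off classification. What does not change, provided the reversal is uniform, is the omnibus Kruskal-Wallis or Friedman p-value; the absolute minimum detectable change is also unaffected. The primary outcomes and the sample size are untouched.

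The practical harm is conditional on literal scoring, which the document neither shows nor excludes. It deserves correction because the FAAM carries all the follow-up evidence, and because enrolment began in July 2023, so forms have probably already been entered.

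The Table 1 wording is a side matter. Higher is better for the YBT (longer reach), the MBESS (30 minus errors) and the FAAM as interpreted, so *reduce* names the wrong direction for those three.

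**What to change.** 1. Correct the item-anchor sentence so that 4 is no problems and 0 is unable. Alternatively, keep the anchors and add an explicit step that recodes each response x as 4 − x before summing.
2. Leave the meaning of 100 and the 90 and 80 cut-offs as they are.
3. Verify that the paper form, the Word documents and the Excel master file all use the corrected direction. Rescore any baseline, post-intervention or follow-up forms that do not. Check every time point, since a mixture of directions would, unlike a uniform reversal, also affect the tests.
4. As a side correction, in Table 1 replace *reduce* with *improve*, noting that higher is better for the YBT, MBESS and FAAM.

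The cost is one sentence, one table cell and a check of the scoring files, plus rescoring only if the check finds reversed forms. No design element, sample size or planned test changes.
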